## Discussion

As consistent, accessible chronic pain management is a huge challenge across the NHS, testing the feasibility of a brief, accessible intervention that could be easily introduced into current NHS practice addresses a key issue in the area of chronic pain research. The usefulness and logistics of implementing a brief self-management intervention into the existing NHS environment is assessed with this study, which has been designed to investigate both acute effects and feasibility. The acute effects will provide an indication of how effective the intervention is and the feasibility assessment will inform the potential likelihood of conducting a definitive randomized controlled trial investigating effectiveness and cost effectiveness of a brief self-help mindfulness tool. Eligibility, recruitment and retention rates will be audited along with resources used in provision of the intervention, including costs of the MP3 players, telephone calls, text messages and staff time needed for intervention delivery. This information alongside patients’ adherence to the treatment regimen, experiences of the intervention, and its acceptability and usefulness will allow for a rigorous and well-designed definitive randomized controlled trial to be conducted if findings are positive.

One of the main limitations of the study is that, for pragmatic reasons, the researcher assessing outcomes is not blinded to the participants’ intervention status. We have attempted to minimize researcher bias by, as far as possible, assessing patient outcomes with validated self-report instruments. Additionally, to further minimize bias, the statistician analysing the data will be blind to the treatment allocation of the participants. It is hoped that a definitive trial would take measures to ensure that the researchers assessing outcomes are blinded to the allocation of participants. Another noteworthy limitation is our inability to monitor patient adherence to the intervention when listening to the audio at home. It is anticipated that, in a full trial, ecological momentary assessment would be used to monitor adherence, including having an audio player that records the level of usage.

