### Aims and objectives

The aim of this paper is to describe the protocol for a pilot randomized controlled trial designed with two primary objectives: assessment of the immediate effects of a brief mindfulness-based intervention on patients with chronic pain and evaluation of the intervention to assess the feasibility of conducting a definitive randomized controlled trial. As regards to the immediate effects of the intervention, it is hypothesized that the intervention will result in a significant reduction in ratings of pain-related symptoms and distress.

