### Randomization

An independent statistician generates a randomization list using the online resource ‘Research Randomizer’. This list is used by researchers to allocate volunteers to either the control or treatment group on a 1:1 basis. Patients are allocated their number in ascending order based on their order of enrolment. Allocation is concealed from the participant and researcher until all baseline assessments have been completed. Due to limited resources, the same researcher delivers the intervention and administers the research measures, and therefore treatment allocation cannot be concealed from the researcher. Thus, neither participants nor researchers are blinded to treatment allocation during intervention delivery or during outcome assessment. An independent statistician, who is blinded to the treatment allocation, will complete the initial analysis for the main outcomes.

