### Procedure in clinic

Patients who meet the inclusion criteria are approached by the research team and given a patient information sheet regarding the study. Patients are given as much time as they want to consider whether they want to participate and written consent is obtained from all patients who agree to do so. Delivery of the intervention is standardized, with a researcher checklist (i.e. written manual) including a step-by-step script developed to address fidelity issues. This script and checklist are used during recruitment and researchers observed each other administering the intervention to at least one patient each so as to standardize procedures.

As detailed previously, an initial face-to-face visit is conducted in a private room or cubicle at St George’s Hospital or St John’s Therapy Centre. Patients are randomized to either the control or treatment group and asked to complete baseline measures, including brief psychological measures, and to listen to the relevant audio once in clinic with the researcher. After listening to the audio, patients are asked to complete the brief psychological measures again. Before leaving, patients are advised to consider barriers and solutions to use of the audio in their own environment and are given a study packet to take home. They are instructed to use the audios as a self-management tool and to try the audio during particularly painful times if possible. The contents of the study packet containing follow-up questionnaires (i.e. Study Diaries 1–3), self-addressed prepaid return envelopes and brief instructions, are then reviewed with the patient in case there are any queries. If the audios are not directly downloaded to a personal device, patients are allowed to keep the MP3 players if they want after they finish, as they are a minimal cost. The offer of the MP3 player is not mentioned in the patient information sheet, and therefore is not considered as an incentive to recruitment.

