#### Brief measures to be completed before and after audio in clinic and the last session during the first week at home

Three brief, single-item measures are used to assess level of distractedness, pain severity and pain distress. Patients are asked to rate “How distracted do you feel right now?” (devised specifically for this study), “How severe are your pain related symptoms right now?”, and “How distressing are your pain related symptoms right now?”, all on a scale from 1 (not at all) to 7 (extremely so).

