### Statistical analysis

We will present the baseline characteristics according to the two study groups. For the analysis assessing the immediate effects of the intervention, we will assess the effect of the body scan versus the control intervention on ratings for the brief psychological measures administered immediately before and after the interventions. This analysis will be conducted for the ‘before’ and ‘after’ ratings in the clinic and also for those conducted in the participant’s own environment. First, we will compute change scores by subtracting post-intervention scores from pre-intervention scores. As it is a pilot study with a small sample size, initially we will assess the effect of the treatment groups on outcomes (i.e. change scores) using *t* tests or Mann–Whitney tests. We will then conduct multiple linear regressions with the change scores as the dependent variables and treatment groups as the independent variable. Statistical significance will be assessed with the likelihood-ratio test, with the estimate of effect given as mean difference of change scores and 95 % confidence interval. As a secondary analysis we will adjust for age, sex and baseline BPI score, as potentially important prognostic baseline factors. We will also inspect the baseline characteristics, for the two groups, to assess whether there are any other potential confounders that need to be controlled for.

Next, we will assess the effect of the study groups on outcomes recorded at baseline and one month. All participants with data at both time points will be included in the analysis. It is unlikely that the study will be sufficiently powered to detect significant differences between the groups but we will carry out analyses in order to inform parameters for a definitive trial. We will compute change scores between baseline and one month for the HADS, EQ-5D-5 L, PCS and the CAMS-R, and we will conduct multiple regressions, with adjustments as above. We will also repeat this procedure for the CAMS-R at baseline and one week.

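### The validated-instrument safeguard is not shown to cover the immediate-effect ratings, and in clinic the post-audio ratings are taken by the unblinded researcher who delivers the audio

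*Protocol article*

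**What the plan says.** The Aims and objectives section gives two primary objectives. The first is "assessment of the immediate effects of a brief mindfulness-based intervention on patients with chronic pain". The Statistical analysis section addresses it by comparing the arms on "ratings for the brief psychological measures administered immediately before and after the interventions", once for the clinic session and once for the session at home. The section on the brief measures describes these outcomes: "Three brief, single-item measures are used to assess level of distractedness, pain severity and pain distress". It says that the distraction item was written for this trial and cites no source for the severity and distress items.

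On blinding, the Randomization section says that "the same researcher delivers the intervention and administers the research measures" and that neither party is blinded during delivery or outcome assessment. Allocation is concealed from both until baseline assessments are complete. Procedure in clinic counts the brief items among the baseline measures and asks the patient "to listen to the relevant audio once in clinic with the researcher", then to repeat the items.

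The Discussion lists as a main limitation that "the researcher assessing outcomes is not blinded to the" participants' allocation. It offers two mitigations. One is the choice of instrument: "We have attempted to minimize researcher bias by, as far as possible, assessing patient outcomes with validated self-report instruments". The other is the blinded statistician, described under Randomization: "An independent statistician, who is blinded to the treatment allocation, will complete the initial analysis for the main outcomes".

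**The concern.** A reader of the Discussion would take it that the patient outcomes in general are protected by validated instruments. The outcomes behind the first primary objective are not shown to have that protection. They are also the outcomes for which, in clinic, the unblinded researcher is closest to the answer. The patient hears a 15-minute recording with the researcher who delivered it, and that researcher then administers the second rating.

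The immediate-effects objective carries the trial's stated hypothesis, and the Sample size section bases its calculation on the distress rating immediately after the intervention. The Discussion plans to use the acute effects as an indication of effectiveness. If patients who have heard the mindfulness audio tend to give a more favourable answer than patients who have heard a book reading, for reasons other than relief, the clinic contrast would mix that tendency with the effect of the audio.

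**Working it through.** The point rests on no figure in the plan, so the check sets the sections side by side.

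**Step 1: which outcomes the safeguard reaches.**

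| Outcome | When rated | Source cited in the article |
|---|---|---|
| HADS, PCS, EQ-5D-5L | Baseline and one month (Table 1 marks HADS at baseline only; the text and Statistical analysis include one month) | Yes |
| CAMS-R | Baseline, one week, one month | Yes |
| BPI | Baseline only; used for adjustment | Yes |
| Distraction item | Before and after audio, clinic and home | None; written for this trial |
| Severity and distress items | Before and after audio, clinic and home | None |

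The instruments with cited sources supply the one-week and one-month comparisons and the baseline covariate. The immediate-effect analysis uses only the last two rows. The follow-up questionnaires are in the take-home packet and are posted back, so the validated follow-up outcomes are also the ones completed away from the researcher.

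**Step 2: exposure of each rating to the unblinded researcher.**

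- Clinic, pre-audio: the researcher is present, but under Randomization neither party yet knows the allocation.
- Clinic, post-audio: both know the allocation, and the researcher who delivered the audio administers the items.
- Home, before and after the last session of the first week: entered in Study Diary 1 away from the researcher. The patient knows which audio was heard.

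The researcher's influence therefore bears mainly on one of these moments, the clinic post-audio rating.

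**Step 3: what this does to the clinic contrast.** The plan defines change as pre minus post. Suppose that response tendency lowers the recorded post-audio score by b_T on average in the treatment arm and by b_C in the control arm, with the pre-audio score unaffected. Then

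expected difference in mean change = true difference + (b_T − b_C).

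A pull common to both arms cancels. A pull that differs by arm does not, because the pre-audio rating contains no matching term to subtract. Adjustment for age, sex and baseline BPI does not address it. Nor does a blinded analysis, since the shift is already in the recorded answer.

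**Step 4: size.** The article gives nothing from which b_T − b_C can be estimated. For scale only, an assumed difference of 0.25 to 0.5 points would be 0.25/1.2 = 21% to 0.5/1.2 = 42% of the 1.2-point difference in the Sample size section. These percentages restate the assumption and are not evidence of bias. The response scale is also unsettled: Baseline data collection gives 1 to 5 and the brief-measures section gives 1 to 7, which must be reconciled.

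**The case against.** The strongest reply is that the limitation is disclosed. The Discussion names the unblinded assessor, Randomization gives limited resources as the reason, and blinded assessors are hoped for in the definitive trial. The safeguard is hedged as an attempt, as far as possible, and the items remain self-report. All of this stands. A reader might infer that the article contradicts itself. It does not; the reassurance is only too general.

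Three further inferences are tempting and not supported:

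- That all three items are unvalidated. The text says only that the distraction item is new. For severity and distress it is silent, and Sample size refers to a perceived distress scale in a previous similar study.
- That every immediate-effect rating is made in front of the unblinded researcher. The home ratings are not, and the pre-audio clinic ratings are described as made under concealment.
- That the validated instruments serve the one-month outcomes only. CAMS-R is also analysed at one week.

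The mechanism can be questioned too. The control is an active audio with the same narrator, similar pace and comparable pauses. Both arms are told to use the audios as a self-management tool, and the full nature of the study is disclosed only at debrief. A difference in response tendency is therefore possible but not shown. The written script and checklist are not reproduced, so they may already say where the researcher is while the patient answers.

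Finally, validation does not itself prevent a courtesy answer. That is correct, and it is why the main remedy below concerns how the answer is collected.

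**Conclusion.** The point holds in a limited form. The validated-instrument safeguard is not shown to cover the three items behind the immediate-effects objective. The clinic post-audio ratings are administered by the unblinded researcher who delivers the audio. A response pull that differs by arm could enter all three clinic change scores, and the blinded statistician could not remove it. Its presence, direction and size cannot be established from the article.

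This assumes that the researcher is near enough to see or receive the answer, as the clinic procedure suggests without saying so, and that concealment operates as described for the pre-audio ratings. The consequence is an avoidable weakness in one contrast of a pilot trial. It does not invalidate the design, but it is worth correcting because the correction needs no extra staff.

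**What to change.** 1. Add to the researcher checklist that the patient completes the clinic post-audio items alone on a separate sheet, with the researcher out of the room or not observing. The patient seals the sheet under the study number, and it is opened only at data entry. If recruitment is under way, record the date of the change.
2. Present the home-diary contrast alongside the clinic contrast and label it as the comparison made without the researcher present. It is not a replicate: it follows a week of use and depends on returned diaries. It does, however, show whether the clinic result appears only when the researcher is there.
3. Reword the Discussion so that the validated-instrument safeguard refers to the one-week CAMS-R and the one-month questionnaires, and not to the brief single items. State that one of those items was written for this trial and, unless a source can be given, that no validation is cited for the other two.

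The cost is a second sheet, envelopes and a line in the existing script. The downside is a few more incomplete items and, if the change is made mid-recruitment, two collection procedures in one dataset.

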### Current study status

Patient recruitment began in January 2015 and is due to be completed in July 2016.

## Abbreviations

BPI, Brief Pain Inventory; CAMS-R, Cognitive and Affective Mindfulness Scale-Revised; EQ-5D-5 L, EuroQol – 5 Dimension – 5 Levels; HADS, Hospital Anxiety and Depression Scale; NHS, National Health Service; PCS, Pain Catastrophizing Scale
